## Analysis population

The following populations will be defined:

- Intention to treat
- Per protocol

## Definition of analyses sets

### Full analysis set

The full analysis set will include data for all patients that are randomised. Where there is less than 10% of data missing, ITT analysis will be performed using mixed effects modelling and standard survival statistics without imputation. For outcomes with more than 10% of data missing, ITT analysis will be performed using multiple imputation and mixed effects models and standard survival statistics. The multiple imputation for each outcome will include all variables considered informative to the censoring mechanism for that outcome.

### Safety analysis set

The safety population will consist of the per-protocol population of patients that received their assigned treatment throughout the trial. Subjects will be included in the per protocol analysis for each outcome if they have complete data at each timepoint for that outcome. Safety data to be analysed will include adverse events, toxicity, and laboratory evaluations. The TROG Independent Data and Safety Monitoring Committee (IDSMC) will evaluate safety data every 6 months to ensure that the trial is safe to continue.

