## Discontinuation of a participant from treatment

Participants may be discontinued from treatment in the following situations:

- Participant decision
- Adverse event
- Severe non-compliance with the study protocol as judged by the investigator and/or TMC.
- Participant incorrectly initiated on study treatment.
- If the treating investigator believes the participant is no longer receiving clinical benefit from treatment and/or requires additional anti-cancer treatment

Study procedures related to SAEs and anti-cancer treatment must be captured until permanent withdrawal from the study.

Participants who stop study involvement prior to the time recommended in the protocol will be requested to continue follow-up visits according to the protocol.

If a participant wishes to stop the study visits, they will continue to receive ongoing care as per their treating team. Study investigators may request an update regarding their ongoing health status via their medical records unless the subject has withdrawn consent.

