## Statistical Analysis Plan

A statistical analysis plan (SAP) will be finalised prior to datalock and contain additional detail on the methods described below.

All analyses will be performed according to an intention-to-treat protocol, with a per-protocol analysis performed as a sensitivity analysis. For the FFLP, PFS, TTP, ORR and OS endpoints, analysis will be performed comparing 2-year estimates from cumulative incidence (FFLP) and Kaplan-Meier survival curves (PFS and OS). The two comparisons between groups (SABR vs. MWA/RFA and SABR vs. SOC) will be analysed separately. Secondary analysis using Gray and log-rank tests will be performed to evaluate differences in overall time to event distributions. Fine and Gray, Cox proportional hazards regression will used to estimate hazard ratios with 95% confidence intervals. Secondary outcomes including the EORTC QLQ-C30 and QLQ-HCC18 (presented as mean scores over time) will be assessed using linear mixed-effects models to account for repeated measures. Additionally, time to deterioration (TTD) of combined GHS/QoL will be analysed. TTD will be defined as the time to first onset of a ≥10 point decrease from baseline. A 2-sided type-1 error rate of alpha=0.05 will be used for all hypothesis testing. All analysis will be performed using Stata software (version 17).

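### The safety set is the per-protocol population with a complete-data rule, so membership depends on events that harm can cause, and the definition conflicts with the intention-to-treat rule

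*Protocol*

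**What the plan says.** Section 14.5.2 defines the safety set: "The safety population will consist of the per-protocol population of patients that received their assigned treatment throughout the trial". It continues: "Subjects will be included in the per protocol analysis for each outcome if they have complete data at each timepoint for that outcome". On content it says: "Safety data to be analysed will include adverse events, toxicity, and laboratory evaluations". The same paragraph says that the independent monitoring committee "will evaluate safety data every 6 months to ensure that the trial is safe to continue".

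Section 14.4 lists the populations to be defined as intention to treat and per protocol only. Section 14.5.1 makes the full analysis set all randomised patients. Section 14.6 says: "All analyses will be performed according to an intention-to-treat protocol, with a per-protocol analysis performed as a sensitivity analysis". Nowhere does the protocol define a set of all treated patients.

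Section 11.1 lists an adverse event among the reasons for stopping treatment, and Section 11.2 lists death and withdrawal of consent as reasons for leaving the study.

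**The concern.** A safety set should hold everyone exposed to a study treatment, whatever happened to them afterwards. Here membership is settled after randomisation, by whether the patient completed the assigned treatment and whether the data are complete. Both can be consequences of toxicity. When a harmed patient leaves the set, the event leaves the numerator and the patient leaves the denominator.

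The arms differ in invasiveness and number of sessions, so the loss may differ between them and could distort the comparison as well as the level. Adverse events are a secondary endpoint (Table 2 and Table 8), and the rationale in Section 1.5 needs a credible toxicity comparison beside the local-control result.

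The complete-data sentence also governs the per-protocol sensitivity analysis of FFLP, PFS and OS, where it does not suit time-to-event outcomes.

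**Working it through.** **1. Who can leave the safety set, and by what route**

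- Stopping treatment for an adverse event (Section 11.1): assigned treatment not received throughout.
- Death or withdrawal of consent (Section 11.2): later timepoints are empty.
- Receiving a modality other than the assigned one: not per protocol. With no treated-patients set in Section 14.4, such a patient has no place in the Section 14.5.2 analysis.
- A missed visit: data not complete at each timepoint.

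The complete-data sentence is worded for the per-protocol analysis. It reaches safety because the safety set is that population.

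**2. Interim reviews.** At a 6-monthly review, no patient still in follow-up has complete data at each timepoint, and treatment throughout the trial cannot yet be judged. Taken literally, the set would be almost empty when the committee needs it.

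**3. The plan's own attrition figures (Section 14.1)**

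- Cohort 1: 47/0.80 = 58.75, so 59 per arm and 118 in total. 118 − 94 = 24 (20.3%).
- Cohort 2: 40/0.80 = 50 per arm and 100 in total. 100 − 80 = 20 (20%).

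These reproduce the stated totals. They count patients not evaluable for 2-year FFLP (10% drop-out plus 10% mortality), not patients lost to safety analysis.

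**4. How much of that 20% could reach the safety set.** This depends on the adverse event window, on which the protocol is inconsistent.

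- *Short window.* Section 13.2.1 reports adverse events to 28 days after the last treatment. Section 6 requires treatment to finish within 42 days of randomisation, so collection ends by day 42 + 28 = 70. Assumption: drop-out and death accrue evenly over 730 days. Loss = 0.20 × 70/730 = 1.9%, about 2 patients in each cohort.
- *Long window.* Section 7.3.2 and Table 4 schedule adverse event reporting at every visit to 24 months and beyond. The full 20% is then a rough upper guide to loss from drop-out and death.

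Laboratory evaluations are also in the safety set. Table 4 schedules bloods at every follow-up visit, so the complete-data rule spans the long schedule for them in either case.

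**5. Effect on a reported toxicity rate (illustration only).** Let f be the fraction excluded, r_in the risk in retained patients and r_ex the risk in excluded patients. The all-patient rate is (1 − f)·r_in + f·r_ex; the safety set reports r_in. The share of affected patients omitted is f·r_ex divided by the all-patient rate. Assume r_in = 5%.

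| r_ex | f = 2%: all-patient rate (share omitted) | f = 20%: all-patient rate (share omitted) |
|---|---|---|
| 5% | 5.0% (2%) | 5% (20%) |
| 20% | 5.3% (8%) | 8% (50%) |
| 50% | 5.9% (17%) | 14% (71%) |

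The safety set reports 5% in every row. The document gives none of these risks.

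**6. Missed visits (illustration only).** Table 4 has 10 adverse event assessments from end of treatment to 24 months (1 + 1 + 8). If each is complete independently with probability 99%, 98%, 95% or 90%, then 90%, 82%, 60% or 35% of patients have all ten.

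**7. Per-protocol efficacy.** Section 14.6 analyses FFLP by cumulative incidence and PFS and OS by Kaplan-Meier. These methods use partial follow-up, so they need no complete-data rule. Applying one can remove censored patients. Over the eight imaging visits to 24 months, per-visit completeness of 98% or 95% leaves 85% or 66%: 100 or 78 of 118 in Cohort 1, against the 94 evaluable patients required. Whether patients with events are also removed depends on the reading: Section 8 ends tumour assessment at progression or death, while Section 7.4 continues assessments beyond progression.

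**The case against.** Four objections have weight.

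- *Toxicity is not confined to this set.* Section 14.6 puts all analyses on an intention-to-treat basis, and adverse event collection in Section 13 is not limited to the per-protocol patients. A reader might infer that harmed patients vanish from every toxicity analysis; the text does not establish that. But the objection only shows that Sections 14.5.2 and 14.6 disagree on which set reports toxicity. It does not make the safety set sound.
- *The 20% is a different quantity.* A reader might infer that 24 and 20 patients will be lost to safety analysis. Those figures belong to 2-year FFLP, and under the 28-day window most later deaths and drop-outs would follow complete adverse event data. This stands.
- *Switching may be uncommon.* The randomised proton-versus-RFA study described in Section 1.4 had 31% and 12.5% not receiving the assigned modality, and a reader might carry those rates over. In its RFA arm, technical unsuitability was found after randomisation. Here suitability for ablation or transarterial therapy is an inclusion criterion (Section 4.3.1) and sets the cohort (Section 5.4.1) beforehand. Treatment courses are also short. The rates do not transfer.
- *A recorded event can count as complete data.* A reader might infer that per-protocol OS and FFLP would approach 100% in both arms. Sections 7.5 and 11 seek vital status even for withdrawn and lost patients, Section 8 asks for assessment at applicable timepoints until progression, and Section 7.4 continues beyond it. That extreme result is not supported.

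It is also fair that greater harm among excluded patients is an inference. If their risk were lower, the set would overstate toxicity.

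**Conclusion.** The definition is wrong as written. It ties the safety set to completing the assigned treatment and to complete data, both of which harm can affect; it conflicts with the intention-to-treat statement; and it cannot be used literally at the interim safety reviews. This is a stated definition, not detail left open for the statistical analysis plan.

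The claim on size is limited: toxicity may be understated, and possibly unequally between arms, by an amount the document cannot supply. The 2% to 20% range covers drop-out and death only. Its lower end assumes even accrual of losses and the 28-day window; its upper end borrows the FFLP allowance under the longer window. Early stopping, switching and missed visits would add to it at rates the protocol does not give.

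On efficacy, the complete-data rule weakens only the per-protocol sensitivity analysis. The primary intention-to-treat comparison of FFLP is untouched.

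**What to change.** In Section 14.5.2, define the safety set as all randomised patients who received any part of a study treatment, grouped by the treatment actually received, with no complete-data condition. Define the per-protocol set separately, by eligibility and delivery of the assigned treatment within the protocol window. Delete the complete-data sentence, and handle incomplete follow-up in the time-to-event analyses by censoring or competing-risk methods.

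State in Section 14.6 that toxicity is reported in the safety set, or otherwise reconcile it with Section 14.5.2, and add the set to the list in Section 14.4. Reconcile the adverse event window in Section 13.2.1 with the visit schedule in Section 7.3.2 and Table 4.

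The population change takes about two sentences in Section 14.5, carried into the statistical analysis plan. It needs no extra patients or data.

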## Statistical Analysis Plan

A statistical analysis plan (SAP) will be finalised prior to datalock and contain additional detail on the methods described below.

All analyses will be performed according to an intention-to-treat protocol, with a per-protocol analysis performed as a sensitivity analysis. For the FFLP, PFS, TTP, ORR and OS endpoints, analysis will be performed comparing 2-year estimates from cumulative incidence (FFLP) and Kaplan-Meier survival curves (PFS and OS). The two comparisons between groups (SABR vs. MWA/RFA and SABR vs. SOC) will be analysed separately. Secondary analysis using Gray and log-rank tests will be performed to evaluate differences in overall time to event distributions. Fine and Gray, Cox proportional hazards regression will used to estimate hazard ratios with 95% confidence intervals. Secondary outcomes including the EORTC QLQ-C30 and QLQ-HCC18 (presented as mean scores over time) will be assessed using linear mixed-effects models to account for repeated measures. Additionally, time to deterioration (TTD) of combined GHS/QoL will be analysed. TTD will be defined as the time to first onset of a ≥10 point decrease from baseline. A 2-sided type-1 error rate of alpha=0.05 will be used for all hypothesis testing. All analysis will be performed using Stata software (version 17).

### Health economics analysis

This study uses a cost-effectiveness analysis to investigate whether the use of SABR represents value for money relative to SOC. The assessment of costs will reflect the use of SABR and its associated comparators, as well as ongoing patient management costs for HCC care (including physician visits, diagnostic and monitoring services, and the management of treatment relative toxicities). Primary hospital service use for the delivery of SABR and conduct of SOC treatments will be recorded through case report form reporting, noting the mode of delivery for SABR, the form of SOC undertaken and whether or not patients received TACE prior to MWA/RFA. Ongoing treatment costs will be assessed using administrative data (Medicare data) for outpatient medical service use (MBS) and pharmaceutical services (PBS). Patient specific costs associated with accessing care, particularly those associated with travel time for attending clinics for care, will also be assessed based on a patient completed questionnaire. In addition, out-of-pocket costs for MBS and PBS use will be estimated based on Medicare data reporting. For each patient, the costs of care will be assessed at the end of follow-up.

Outcomes for the cost-effectiveness analysis include the difference in the proportion of patients with FFLP at two years, and the difference in quality adjusted life years (QALYS) observed over the study period. In the first instance, outcomes will be expressed based on the primary outcome, the two-year FFLP rate, and the cost-effectiveness expressed as the cost per additional patient with local control at two years. QALYs, the combined impact of the impact of HCC and its treatment on survival and quality of life, will be assessed using patient completed information from the EORTC QLQ-C30. Thus, responses to that questionnaire, will be converted to values on a preference scale – 0 to 1 and applied to survival time to estimate QALYs, allowing the cost per QALY gained for SABR compared with SOC at two years to be estimated.

The base case analysis will adjust for the effect on OS of crossover post-progression. The potential for costs and outcomes to extend beyond the duration of the trial, and the resulting impact on the cost per QALY, will be explored in a modelled analysis. Cost-effectiveness will be estimated for each of the patient cohorts separately (PA eligible and stage migration patients, respectively) and for an overall weighted analysis based on the proportion of early inoperable HCC patients in Australia anticipated to fall into these two groups.

## Secondary Analysis

TROG encourages secondary analysis and TROG Policy Statement E12 *Secondary Analyses in TROG Clinical Trials* outlines the procedures for this.

There is an intent to undertake and facilitate ad hoc secondary analyses with data collected during the trial.

Participants on this study will be asked to grant advanced permission for the possible future sharing of the data collected in this study. Additional participant consent for use of the data will only be sort if it is a requirement of the HREC.

# STUDY AND DATA MANAGEMENT

## Participating Centres

The Principal Investigator at each centre should comply with all the terms, conditions, and obligations of the Clinical Trial Research Agreement (CTRA), or equivalent, for this study. In the event of any inconsistency between this Clinical Study Protocol and the CTRA, the terms of Clinical Study Protocol shall prevail with respect to the conduct of the study and the treatment of participants and in all other respects, not relating to study conduct or treatment of participants, the terms of the CTRA shall prevail.

Before activating the trial, participating sites are required to sign an agreement accepting responsibility for all trial activity which takes place within their site.

Once the CTRA has been signed by all required signatories, the required trial documentation is in place and a site initiation (visit or teleconference) has taken place, notification of site activation will be issued to the PI and other applicable site staff.

**Sites must not approach any potential participant until they have received the activation notification.**

## Training of study site personnel

Before the first participant is entered into the study, training will be provided on the requirements of the Clinical Study Protocol and related documents with the investigational staff and training in any study specific procedures.

The Principal Investigator will ensure that appropriate training relevant to the study is provided to their study team, and that any new information relevant to the performance of this study is forwarded to the staff involved.

The Principal Investigator will maintain a record of all individuals involved in the study (medical, nursing and other staff).

### Radiotherapy

Each centre will complete radiotherapy quality assurance procedures, as described in Section 6.3 and the **SOCRATES HCC Quality Assurance (QA), RT Planning and Delivery Guidelines**, prior to commencing recruitment. The quality assurance programme will continue throughout the trial, with investigator training as required.

## Monitoring of the study

During the study, the central trial coordinator will have regular contact with the site to:

- Provide information and support to the Investigator(s)
- Confirm that facilities remain acceptable
- Confirm that the investigational team is adhering to the protocol, that data is being accurately and timely recorded in the CRFs and accountability checks are being performed

### Site visits

If a monitoring visit is required, TROG will contact the site to arrange the visit. Once a date has been confirmed, the site should ensure that full medical records of participants selected for source data verification are available for monitoring.

TROG staff conducting on-site monitoring will review essential documentation and carry out source data verification to confirm compliance with the clinical trial agreement and trial protocol. If any problems are detected during the monitoring visit, TROG will work with the Principal Investigator/s or delegated individual to resolve issues and determine appropriate action.

### Audit or inspection

Authorised representatives of the Sponsor, funder, applicable regulatory authorities, or an Ethics Committee may perform audits or inspections at the centre, including source data verification. The purpose of an audit or inspection is to systematically and independently examine all study related activities and documents, to determine whether these activities were conducted, and data were recorded, analysed, and accurately reported according to the protocol, Good Clinical Practice (GCP), guidelines of the International Conference on Harmonisation (ICH), and any applicable regulatory requirements. The Investigator will contact TROG immediately if contacted by a regulatory agency about an inspection at the centre.

### Archiving of study documents

Essential trial documents and source documentation (including medical history, radiological imaging, laboratory tests, treatment records, verification films and portal images) must be retained for at least 15 years after completion of the trial in accordance with ICH GCP Guidelines. Documents should be securely stored and access restricted to authorised personnel.

### Regulatory reviews

The TCC will be responsible for collecting, maintaining and monitoring all required essential documentation from the Trial Site before, during and after the conduct of the trial.

## Study timetable and end of study

The end of the study is defined as the last visit of the last participant undergoing the study.

The study may be terminated at individual centres if the study procedures are not being performed according to GCP, or if recruitment is slow. TROG may also terminate the entire study prematurely if concerns for safety arise within this study or from any other study with similar interventions.

## Data acquisition and management

Case Report Forms (CRF) will be used for the collection of trial data. The TCC will provide guidance to sites to aid the completion of the CRFs.

The TMC reserves the right to amend or add to the CRF template suite as appropriate. Such changes do not constitute a protocol amendment, and revised or additional forms should be used by sites in accordance with the guidelines provided by the TCC.

The investigator will ensure that the data are recorded in the Case Report Forms as specified in the study protocol and in accordance with the instructions provided. The investigator ensures the accuracy, completeness and timeliness of the data recorded and of the provision of answers to data queries according to the Clinical Study Agreement. The investigator will sign the completed Case Report Form at the end of the study.

## Security and back up of data

All study data will be stored securely either in locked rooms or on a secure server at trial site and the TCC. Access to the study data will be restricted to trial staff. In addition, Site Trial Coordinators will only have access to their own centre’s data. At the TCC a password system will be utilised to control access to the trial database and only those staff members who will be working on this study will be allocated access to this trial. All reports prepared will be prepared such that no individual participant can be identified.

An independent external back-up and disaster recovery system that ‘mirror replicates’ a copy of all data saved in real-time is in place at the TROG Central Operations Office. The back-up server is located off-site in a climate-controlled facility and will be retained indefinitely.

